Specific brain structures with possible impacts on gait recovery in IS patients will be identified using functional magnetic resonance imaging (fMRI) during simple lower limb movements, gait imagery, and gait observation as well as using diffusion-weighted imaging (DWI) and surface-based morphometry. The functional MRI activation magnitude, calculated as the difference in the BOLD signal between task and rest, will be assessed within predefined gait-related brain regions of interest (ROIs), i.e., the sensorimotor cortex, premotor cortex, supplementary motor area, brainstem, and cerebellum. Changes in these ROI parameters over time will be statistically tested within the group, and the regional post-training minus pretraining difference in each group will be submitted to a between-group analysis. Gait recovery after treadmill exercise has been associated with increased task-related activation in the posterior cerebellum and brainstem [28] as well as in the primary sensorimotor cortices and basal ganglia [29]. Moreover, the task-related activation volume in the ipsilesional primary sensorimotor foot representation has been identified as an independent baseline predictor of gait recovery [30]. However, simple leg movements may not be sufficiently representative of a more complex motor behavior such as gait. As it is impossible to directly measure gait-related brain activation in fMRI, gait imagery has been employed as a substitute for real movements in healthy subjects [31] as well as stroke patients with gait impairment [32]. Beyond fMRI, other potential imaging biomarkers include white matter integrity, assessed using diffusion-weighted imaging (DWI), and surface-based morphometry based on structural imaging [33]. So far, according to systematic reviews, evidence for biomarkers based on fMRI, DWI, and structural MRI data remains inconclusive, mostly due to methodological limitations [16].

-Neurological impairment

The National Institute of Health Stroke Scale (NIHSS) represents the most widely used rating scale to evaluate neurological impairment after IS [34]. The NIHSS includes items on consciousness, language, movement, sensation, ataxia, eye movement, the visual field, and others. The scores range from 0 to 42, with higher scores indicating more severe neurological deficits.

-Sensorimotor impairment

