### 2.7. Sample Size

Based on an analysis of our pilot data concerning the gait velocity (primary outcome), 120 participants (60 in each group) are anticipated to be enrolled in this study. This number of participants would provide 85% power (α level 5%) to detect a difference of 0.16 m/s in the 10 MWT (with respect to a missing data rate of 15% and an expected 10% drop in the follow-ups) between groups after intensive rehabilitation with add-on intervention. The gait speed difference of over 0.16 m/s was previously defined as the minimal clinically important difference in gait speed in subacute stroke patients [46].

For the multimodal magnetic resonance imaging (MRI), including functional MRI (fMRI), we have estimated that a sample size of 50 participants (25 in each group) will suffice to find significant correlations of MRI outcomes with gait recovery. This is based on previous studies of fMRI and gait recovery in similar clinical cohorts [29,32]. We will perform multimodal MRI in half of the randomly selected enrolled IS patients (1:2 randomization), i.e., in 60 participants, to allow for a common drop-out of examined patients with MR images of poor or insufficient quality. As we do not have sufficient information to estimate the variance in the outcomes, we plan to calculate the definitive effect sizes based on the interim analysis of the first 30 subjects measured within all four visits (visit 1–visit 4).

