### 2.10. Statistical Analysis

For the statistical analysis of all tested clinical parameters, gait movement pattern parameters, and extracted imaging parameters, the distribution of the data will first be explored. If normally distributed, a two-factor mixed-model ANOVA will explore the differences between the groups and time points. If not normally distributed, Friedman tests will be used to explore the differences between time points (visits 1–4) within each group and Mann–Whitney U tests will be used to explore the differences between both groups (RTGT and TTGT).

The statistical analysis of fMRI data will include standard preprocessing with subsequent general linear model fitting and a group-wise analysis in the Montreal Neurological Institute (MNI) 152 standard space after the nonlinear normalization of the individual structural MRI data [49]. Significant group effects will be evaluated using an analysis of covariance (ANCOVA) with group, visit, and age as covariates. An atlas-based region of interest (ROI) analysis will be used to evaluate the amplitude and volume of the primary sensorimotor and premotor activations and the laterality index (ipsilesional − contralesional/ipsilesional + contralesional), which are the main secondary outcome measures of the fMRI analysis. Since the functional study design and paradigm partly follow the study of Boyne et al. [32], the choice of regressors and contrasts for the statistical analysis of the corresponding data will likewise follow that study. Structural data (DWI and T1-weighted) will be evaluated in separate pipelines to extract the following parameters from anatomically defined ROIs: regional cortical thickness; fractional anisotropy (FA); and axial, radial, and mean diffusivity (AD, RD, and MD), respectively. Alternative DWI analysis models may include, e.g., FD/FDC or NODDI. The quantitative parameters derived from functional and structural imaging will be included in an extended factor analysis of the global predictors of gait recovery.

With respect to the type of missing variable, the appropriate imputation (e.g., single imputation, multiple imputation, etc.) might be performed if needed [50].

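### Sections 2.6.2 and 2.10 define the fMRI secondary outcome by two different sets of measures and tests, so either could be reported as the planned one

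*Protocol article*

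**What the plan says.** **Section 2.6.2 (Secondary Outcomes, brain activity).** Imaging uses "functional magnetic resonance imaging (fMRI) during simple lower limb movements, gait imagery, and gait observation". The outcome is then defined: "The functional MRI activation magnitude, calculated as the difference in the BOLD signal between task and rest, will be assessed within predefined gait-related brain regions". Five regions are listed: "the sensorimotor cortex, premotor cortex, supplementary motor area, brainstem, and cerebellum". On testing: "Changes in these ROI parameters over time will be statistically tested within the group, and the regional post-training minus pretraining difference in each group" goes forward to a between-group analysis.

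**Section 2.10 (Statistical Analysis).** The atlas-based region analysis is to evaluate "the amplitude and volume of the primary sensorimotor and premotor activations and the laterality index", "which are the main secondary outcome measures of the fMRI analysis". The model is: "Significant group effects will be evaluated using an analysis of covariance (ANCOVA) with group, visit, and age as covariates". The opening paragraph of the same section also applies its general rule to extracted imaging parameters: two-factor mixed ANOVA if normally distributed, otherwise Friedman and Mann–Whitney tests.

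**Section 2.7 (Sample Size).** Fifty participants, 25 per group, "will suffice to find significant correlations of MRI outcomes with gait recovery". Sixty are to be scanned.

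**Table 2** lists fMRI as a secondary outcome under its generic name only, so it does not decide between the two definitions.

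**Interim analysis (end of section 2.10).** A look at the first 30 fully measured participants is to steer the final statistical methods, and the principal investigator will have access to the results.

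**The concern.** A secondary outcome named in advance should be the same outcome wherever it appears. Here it is not. A between-group difference confined to the cerebellum would be a planned result under section 2.6.2 and outside the main measures under section 2.10. A difference in the laterality index would be a main result under section 2.10 and absent from the outcome as section 2.6.2 defines it. The between-group test differs as well.

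What is at stake is selective reporting. With two definitions in force, whichever gives the more striking result can be described truthfully as planned. The interim analysis makes this more than a drafting matter, because the methods may be settled after some of the data have been seen. Section 2.9 plans no access to the full protocol or the statistical code, so a later reader would mostly have this article to judge by.

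**Working it through.** **Step 1. The two definitions side by side**

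| | Section 2.6.2 | Section 2.10 |
|---|---|---|
| Metric | Magnitude (task minus rest) | Amplitude, volume, laterality index |
| Regions | Sensorimotor, premotor, supplementary motor area, brainstem, cerebellum | Primary sensorimotor, premotor |
| Between-group test | Comparison of post-minus-pre change | ANCOVA with group, visit and age; also mixed ANOVA or rank tests for extracted imaging parameters |
| Status | Secondary outcome | Main fMRI measures |

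Take amplitude and magnitude as the same quantity and the two sensorimotor labels as the same region, which is the reading kindest to the plan. Section 2.6.2 then has 5 measures. Section 2.10 has 2 amplitudes + 2 volumes + 1 laterality index = 5. Two are shared, so the union is 5 + 5 − 2 = 8 (9 if laterality is computed per region). Neither list contains the other: section 2.10 adds volume and laterality, and section 2.6.2 adds three regions.

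The tests also answer different questions. A comparison of change isolates what happened between two visits. A group effect with visit as a covariate, as worded, is a difference across the visits entered, and no group-by-visit term is named.

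**Step 2. The plan's own figure**

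The plan gives no error rate for the fMRI outcome. Its one imaging figure, 50 participants, cannot be reproduced, because no correlation, effect size, standard deviation or power accompanies it. For orientation, with n = 50, two-sided 5% and an assumed 80% power, the detectable correlation is tanh[(1.960 + 0.842)/√47] = 0.39.

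**Step 3. Chance of at least one false between-group result**

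Assumptions: no true difference, each measure tested once at two-sided 5%, and test statistics normal with a common correlation ρ. The documents give no value for ρ.

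- Independent tests: 1 − 0.95^k. For k = 5: 1 − 0.95^5 = 22.6%.
- Correlated tests: 1 − ∫ [Φ((c − √ρ·u)/√(1−ρ)) − Φ((−c − √ρ·u)/√(1−ρ))]^k φ(u) du, with c = 1.960.

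| Tests assumed | k | Independent | ρ = 0.5 | ρ = 0.8 |
|---|---|---|---|---|
| Section 2.10 list, one task | 5 | 22.6% | 18.3% | 12.7% |
| Both lists, one task | 8 | 33.7% | 25.0% | 15.7% |
| One list, three tasks | 15 | 53.7% | 36.1% | 20.2% |
| Both lists, three tasks | 24 | 70.8% | 45.8% | 23.8% |

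The first row is the closest to what the plan labels as main. The other rows show how the rate grows if the ambiguity is used in full; the document does not say that all those tests will be run as confirmatory comparisons.

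**Step 4. What control would cost**

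Holm over five measures compares the smallest p-value with 0.05/5 = 0.01. With 25 per group and an assumed 80% power, the detectable standardised difference at that step is (2.576 + 0.842) × √(2/25) = 0.97, against (1.960 + 0.842) × √(2/25) = 0.79 at 5%. For a correlation with n = 50, the smallest significant value rises from 0.28 to 0.36.

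**The case against.** The best defence is that the sections describe a broad set of regions and, within it, a main subset. A result can be planned without being main, so the cerebellar example would be no conflict. The word main does give a partial ranking, and it would be wrong to say there is no hierarchy at all. The defence still fails on content: a subset cannot contain measures that the full set lacks, and volume and laterality are not in the section 2.6.2 definition. Activation volume does appear in that section, but as a predictor found in earlier work, not as an outcome of this trial.

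A second objection stands. This is a condensed article and the analysis plan is not shown. How multiplicity is handled across secondary imaging measures is commonly left to that plan, so its absence here is not a defect in itself.

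A third stands in part. Section 2.10 says that regressors and contrasts for the corresponding data follow a cited study, which may narrow the tasks and contrasts. That source is not at hand, so the three-task rows are an assumption. It would not reconcile the two lists in this article.

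The imaging aims are also hedged as possible predictors, and the outcome is secondary, measured in 60 of 120 participants.

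**Conclusion.** The inconsistency is real and can be seen in the text without any calculation: two partly overlapping lists, more than one between-group test, and only two measures in common. It should be reconciled.

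For the five section 2.10 measures in one task, unadjusted testing carries about a 13% to 23% chance of at least one false between-group result, against 5% for one test. This rests on assumed correlations from 0.8 down to zero and one test per measure.

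A reader might infer that a chance finding is likely. The documents do not support that. The rate passes one half only when all three tasks are counted and correlation is low, and the 24-test family is built by joining the lists rather than specified anywhere. At correlation 0.5 even that family gives 46%. Nor do the figures cover false predictors of gait recovery, since only between-group tests were counted.

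The gait-speed primary outcome is unaffected.

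**What to change.** Before any imaging data are seen by arm, including at the interim analysis:

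1. Put one identical list of main fMRI measures in sections 2.6.2 and 2.10, stating the task or tasks to which it applies.
2. Give one between-group test and one visit contrast for that list, for example the difference between groups in change from visit 1 to visit 2. Remove or subordinate the competing models.
3. Either control the error rate within the short list, for example by Holm, or name a lead measure tested at 5%. Reducing the outcome to a single task, region and metric is one way to do this, but it is a design choice and not required.
4. Label all other region, task, volume, laterality, diffusion and cortical-thickness results exploratory, and align the correlation claim in section 2.7 with the list.

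The cost is wording, with no extra scans or patients. The downside is a stricter threshold if several measures stay on the list (a detectable difference of up to 0.97 rather than 0.79 standard deviations for five measures, as worked above), and more imaging results become hypothesis-generating. A single lead measure avoids the stricter threshold.

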### 2.5. Study Protocol

All enrolled participants will be examined by evaluators that will be blinded to the group allocation. The assessments will be realized by certified neurologists, rehabilitation physicians, physiotherapists, and biomedical engineers with respect to their specialization at four assessment timepoints. Clinical visits will occur as follows:

Visit 0 (T0): enrolment 5–10 days after onset of qualifying IS at the Comprehensive Stroke Centre.

Visit 1 (T1) (3–5 days after V0): assessment before the initiation of an intensive rehabilitation program including assisted gait training (RTGT or TTGT) at the Department of Rehabilitation.

Visit 2 (T2) (14 ± 7 days after visit 1 and 1 month after visit 0): assessment at the end of the intensive rehabilitation program including gait training at the Department of Rehabilitation.

Visit 3 (T3): assessment 12 ± 1 weeks after visit 0 (3 months after visit 0).

Visit 4 (T4): assessment 24 ± 2 weeks after visit 0 (6 months after visit 0).

Scheduled outpatient visits in the GAITFAST trial will be performed by a neurologist at the Department of Neurology (visit 1–visit 4), a rehabilitation physician, a physiotherapist, and a biomedical engineer at the Kinesiology Laboratory at the Department of Rehabilitation (visit 1–visit 4). Multimodal MRI data will be acquired on a 3T scanner (Siemens Magnetom Vida, Erlangen, Germany) at the Department of Radiology. Scanning will be supervised by a member of the Functional Magnetic Resonance Imaging Laboratory (visit 1–visit 4). The duration of patient participation will be 6 months (Table 1).

Each visit will include an assessment to evaluate gait speed, gait dependency, neurological impairment, sensorimotor function, and gait biomechanics and a multimodal MRI of the brain. The outcome variables and study flow are presented in more detail in Table 2.

As data accumulate, the validity and the integrity of the trial will be subjected to an interim analysis after the first 30 participants have been assessed at all four assessment timepoints. With respect to the results of the interim analysis, the study design (such as the sample size, allocation ratio, or eligibility criteria) might be adaptively modified.

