Adverse events (e.g., falls, pain, or dizziness) that occur during the study period, whether related to the study intervention or not, will be recorded. In case the training intervention is discontinued for any reason (e.g., hospital discharge, medical complications, or serious adverse event), a participant will not be required to participate in the follow-up assessments. Patients who suffer from a recurrent stroke during the study will be excluded, as will those with any medical condition or disease that occurs during the study and may affect limb movement or mobility. All enrolled patients may undergo outpatient rehabilitation after discharge from the Department of Rehabilitation. The types of rehabilitation treatment during follow-up will be recorded.

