### 2.8. Randomization

The randomization of the enrolled participants for robot-assisted treadmill gait training (RTGT) or therapist-assisted treadmill gait training (TTGT) will be performed as a block randomization with a 1:1 allocation to either RRGT or TTGT. As mentioned above, in randomly selected IS patients with a 1:2 allocation, a repeated multimodal magnetic resonance imaging (MRI) examination, including functional MRI (fMRI), will be performed during the study follow-up.

Participants will be randomized after the screening of eligible participants by the certificated neurologist at the Comprehensive Stroke Centre and before the first clinical visit (visit 1).

Participants will be randomized in a 1:1 ratio and in a 1:2 ratio to multimodal magnetic resonance imaging (MRI) using the web randomization module. A randomized web number generator will be implemented for group allocation. Neurologists will generate the allocation sequences, enroll the participants, and assign the participants to interventions.

The allocation might be adaptively modified in cases when patients randomized for RTGT, after enrolment and during the course of rehabilitation, will be identified as independent walkers (FAC > 3). This change will be reported. It has previously been identified that stroke survivors with gait deficits (FAC ≤ 3) with higher motor impairment are those who benefit the most from robot-assisted therapy in combination with conventional therapy [15,23,47,48].

All participating patients will obtain a card before discharge (visit 2) with the dates of all scheduled outpatient events (visit 3 and visit 4), including the dates of the fMRI examinations and even the telephone contacts with the study investigators (neurologist and principal physiotherapist). All enrolled patients will be promoted and motivated to remain in the study and complete follow-ups during each scheduled visit. In participants who discontinue or deviate from the intervention protocols, the acquired outcome data will be collected for a further subanalysis.

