As data accumulate, the validity and the integrity of the trial will be subjected to an interim analysis after the first 30 participants have been assessed at all four timepoints. The interim analysis, including the first 30 completely measured participants, will guide the final statistical methods. An interim analysis based on 30 participants with complete data will be conducted to perform a power analysis and to compute the final sample size. The principal investigator will have access to the interim results. Additional analyses and further subgroupings are not planned.

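### The sample-size recalculation uses only 30 four-visit completers, so it discards usable visit 2 gait speeds and cannot check the loss allowance from those records

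*Protocol article*

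**What the plan says.** Section 2.5 triggers an "interim analysis after the first 30 participants have been assessed at all four assessment timepoints" and says that, depending on the result, "the study design (such as the sample size, allocation ratio, or eligibility criteria) might be adaptively modified". Section 2.10 repeats the trigger and gives the set two uses. One is the sample size: "An interim analysis based on 30 participants with complete data will be conducted to perform a power analysis and to compute the final sample size". Its second use is the choice of methods: "The interim analysis, including the first 30 completely measured participants, will guide the final statistical methods".

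Section 2.7 plans 120 participants (60 per group) for 85% power at a 5% level to detect 0.16 m/s on the 10-metre walk between groups after the intensive rehabilitation, "with respect to a missing data rate of 15% and an expected 10% drop in the follow-ups". The pilot SD behind 120 is not printed.

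Three statements bear on who can reach four visits. In section 2.5, when training is discontinued, "a participant will not be required to participate in the follow-up assessments". The same section adds: "Patients who suffer from a recurrent stroke during the study will be excluded", together with those who develop a new condition that may affect mobility. In section 2.8, for participants who discontinue or deviate, "the acquired outcome data will be collected for a further subanalysis".

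**The concern.** Entry to the interim set depends on an event six months after the start, while the powered comparison is made after about two weeks. Two consequences follow.

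First, the SD that resets the sample size comes from people who stayed to visit 4. The reasons the article gives for leaving include medical complications, serious adverse events, recurrent stroke and new mobility problems, so a link between loss and gait speed is plausible. If there is one, the SD among completers need not equal the SD among those analysed at visit 2.

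Second, 120 rests on two loss figures, and the interim is the natural place to check them. A set made up only of completers shows no loss by construction.

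What is at stake is the final sample size, which is hard to correct once recruitment has closed.

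**Working it through.** **Inputs.** From section 2.7: N = 120 (60 per group), power 85%, level 5%, difference 0.16 m/s, losses 15% and 10%. From sections 2.5 and 2.10: 30 completers. Assumptions: two-sided test, normal approximation, z-sum 1.960 + 1.036 = 2.996.

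**1. The plan's own figure.** Because the SD is not given, 120 cannot be reproduced, only solved backwards with SD = (0.16 / 2.996) × √(n/2), where n is the number analysed per group.
- Losses multiplied: 60 × 0.85 × 0.90 = 45.9, SD = 0.256 m/s.
- Losses added: 60 × 0.75 = 45, SD = 0.253 m/s.
- No loss: n = 60, SD = 0.293 m/s.

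**2. Who falls outside the set.** 30 / 0.765 = 39.2 and 30 / 0.75 = 40. At the planned losses, 39-40 are enrolled to obtain 30 completers, and 9-10 are left out. Those counts do show the loss: 9/39 = 23% (exact 95% interval 11% to 39%).

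**3. Selection effect on the SD.** Simulation of a normal outcome with 23.5% lost, where rho is the correlation between loss and gait speed:

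| Pattern of loss | Completer SD / full SD |
|---|---|
| Unrelated (rho 0) | 1.00 |
| Slower walkers, rho 0.3 | 0.98 |
| Slower walkers, rho 0.5 | 0.94 |
| Exactly the slowest lost | 0.74 |
| Middle of the range lost | 1.14 |

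The effect can be nil, and it can go either way.

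**4. Effect on power, loss allowance kept.** Let completers have SD 0.256, let non-completers differ in mean by d, and let a share f of non-completers be analysed at the powered visit. Then:
- n = 60 × (0.765 + 0.235f)
- p = 0.235f / (0.765 + 0.235f)
- variance V = 0.256² + p(1 − p)d²
- power = Φ(0.16 / √(2V/n) − 1.96)

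| d (m/s) | f = 0 | f = 0.25 | f = 0.5 | f = 1 |
|---|---|---|---|---|
| 0.1 | 85% | 87% | 89% | 92% |
| 0.2 | 85% | 86% | 87.5% | 90% |
| 0.3 | 85% | 84.5% | 85% | 87% |

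Example, d = 0.3 and f = 1: V = 0.0654 + 0.235 × 0.765 × 0.09 = 0.0816; standard error √(2 × 0.0816 / 60) = 0.0522; 0.16 / 0.0522 = 3.07; Φ(1.11) = 87%. The lowest value over all f is about 84.5%, also with losses added to 25%.

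**5. Effect on power if loss were taken as 0%.** With SD 0.256, 92 evaluable would become 92 enrolled. After 23.5% loss, 46 × 0.765 = 35.2 per group; standard error 0.256 × √(2/35.2) = 0.061; 0.16 / 0.061 = 2.62; Φ(0.66) = 75%.

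**6. Precision of the SD.** With 30 people in two groups (28 degrees of freedom), the 95% interval is 0.79 to 1.35 times the true SD. Squared, that is 0.63 to 1.83 times the right sample size, or about 76 to 219 against 120. At moderate rho, this exceeds the selection effect in step 3.

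**The case against.** The strongest reply is that the harm is small. A reader might compute power by putting the variance of all patients (step 4 with f = 1) over 45-46 analysed per group, which gives about 84%, 81% and 76-77% for gaps of 0.1, 0.2 and 0.3 m/s. That counts the same patients twice: they are absent from n and present in the variance. If non-completers are not analysed, the completer SD is the right one. If they are analysed, n rises with them. This objection stands in full.

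A reader might also infer that everyone who stops training is left out. Section 2.5 does not require follow-up after stopping, but it does not bar it. Section 2.8 says all enrolled patients are encouraged to complete follow-up. Someone who stops training and attends every visit can be among the 30.

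Nor do the documents show that the loss rate will be misjudged. It can be read from the enrolment count, section 2.9 promises to report missing data, and nothing says that the allowances in section 2.7 are dropped.

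Four-visit data also have a purpose. The endpoint is described as recovery up to six months, and the planned mixed-model ANOVA needs the within-person covariance across visits. Section 2.7 mentions the 30 in its MRI paragraph, but section 2.10 does not limit the recalculation to MRI.

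Finally, an article may leave the details of a recalculation to the full protocol. That covers how losses enter. It does not cover the choice of set, which the article fixes explicitly.

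**Conclusion.** The point holds in a limited form. As written, the recalculation discards visit 2 gait speed from participants lost later, selects the SD on completion, and uses records that cannot by themselves test the 15% and 10% allowances.

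With the loss allowance kept, no power below about 84.5% is shown for gaps up to 0.3 m/s. These gaps are assumptions, as are the two-sided test and the back-solved SD of 0.253-0.256 m/s. Only an extreme such as losing exactly the slowest walkers would do much more, and nothing in the article supports it. The 75% figure applies only if loss were set to zero, which the article does not say. The reading of the powered contrast as visit 2 rests on the wording of section 2.7.

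The case for change is that the stated rule wastes relevant data on an SD that is already imprecise, and that a better rule costs almost nothing.

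**What to change.** Replace the set defined by completion with one defined by randomisation order, for example the first 40 randomised participants whose visit 4 date has passed, whether or not they completed. Then:
- estimate the pooled gait-speed SD from everyone in that set with the powered visit measured;
- take the loss rate as the share of those randomised without that measurement;
- carry that loss rate into the recalculated size;
- use the four-visit completers only for the within-person covariance.

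This takes a few lines of protocol wording, needs no new data, and falls at about the same calendar time, since 30 completers already imply 39-40 enrolled. The gain in precision is modest, because at most about ten measurements are added. The downside is that the recalculated size may be slightly less favourable.
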